### 3.2 Secondary Endpoints

---

#### Multiple Myeloma

For MM, efficacy will be evaluated per adapted International Myeloma Working Group (IMWG) criteria:

- Overall response rate (ORR), defined as partial response (PR) + very good partial response (VGPR) + complete remission (CR) + stringent complete response (sCR).
- Clinical benefit rate (CBR), defined as minimal response (MR) + PR + VGPR + CR + sCR.

Duration of response (DOR), defined as the time between date of first response and the first occurrence of progression or death from any cause, whichever occurs first.

## Acute Myeloid Leukemia

For AML, efficacy will be evaluated per adapted International Working Group (IWG) and European Leukemia Net (ELN) criteria:

- Composite complete remission (CRc), comprised of CR + CR with incomplete blood count recovery (CRi).
- CR + CR with partial hematologic recovery (CRh).
- ORR, comprised of CRc + PR.
- DOR, as defined above.

### 3.3 Additional Efficacy Endpoints

---

Overall survival will be assessed as an exploratory efficacy endpoint of the study.

### 3.4 Biomarker Research Endpoints

---

Biospecimens (whole blood, plasma, bone marrow aspirate, and/or bone marrow core biopsies) will be collected at specified time points ([Appendix D](#)) throughout the study to evaluate known and/or novel disease-related or drug-related biomarkers in circulation or at tissue sites. The types of biomarkers to be analyzed may include, but are not limited to, nucleic acids, proteins, lipids, and/or metabolites, either free or in association with specific cell types.

Types of biomarker analyses may include, but are not limited to, determination of MCL-1, BCL-2, and BCL-XL expression or functional dependence, depth of responses as measured by MRD techniques, and assessment of mutation status in MM and AML. These assessments may be explored in the context of MM, AML, or related conditions and/or ABBV-467 or drugs of similar classes. This research may be exploratory in nature and the results may not be included with the clinical study report. Biomarker samples will be collected and analyzed from all subjects, unless precluded by local regulations or restrictions.

Further details regarding the biomarker research collection time points are located in Section 3.8 of the Operations Manual ([Appendix J](#)).

## 4 INVESTIGATIONAL PLAN

### 4.1 Overall Study Design and Plan

---

This is a Phase 1, first-in-human, open-label, dose escalation and dose expansion study evaluating ABBV-467 in subjects with R/R MM and R/R AML; the schematic of the study is shown in [Figure 1](#). Further details regarding study procedures are located in the Operations Manual. See [Section 5](#) for information regarding eligibility criteria. Dosing will be weekly, on a 28-day cycle, though alternative

dosing frequencies may be studied if supported by the totality of safety, efficacy, PK, and/or pharmacodynamic (PD) data.

Subjects will continue ABBV-467 therapy until disease progression, unacceptable toxicity, or withdrawal of consent. No subject will receive ABBV-467 for longer than 24 months within the context of this study.

**Figure 1. Study Diagram**

[figure not shown]

AML = acute myeloid leukemia; MM = multiple myeloma; PD = pharmacodynamic; PK = pharmacokinetic;

RP2D = recommended Phase 2 dose; R/R = relapsed/refractory

Note: Part C will be initiated after a pharmacologically and/or clinically active and tolerable dose is determined in Part A. The expansion component will target enrollment of 20 response-evaluable subjects (with a maximum of 24 subjects enrolled).

## Dose Escalation Guidelines

The goal of the dose escalation is to find the RP2D. The dose-escalation stage allows characterization of safety, tolerability, efficacy, PK, and PD data for each dose level while respecting the de-escalation and dose-elimination boundaries specified by the Bayesian optimal interval (BOIN) design. To maintain subject safety, all dose escalation parts will be guided by BOIN design based on the cumulative number of subjects who experience a dose-limiting toxicity (DLT) in a given ABBV-467 dose level. De-escalation and dose elimination will occur when instructed by the BOIN rules set forth in Table 1. However, if the BOIN rules recommend dose escalation or dose de-escalation, the escalation or de-escalation decision will be made in consideration of all available information. No new subjects would be added to the dose escalation stage after a maximum of 12 subjects enrolled in a single dose level.

Dose escalation decisions require a minimum of 2 DLT-evaluable subjects in dose levels 1 and 2, and a minimum of 3 DLT-evaluable subjects for all subsequent dose levels. For this study, the DLT observation period is defined as the first treatment cycle (Cycle 1, 28 days). Adverse events occurring after the DLT

observation period will also be reviewed and may be taken into consideration for ensuring dose escalation decisions. At least 6 subjects will be treated during dose escalation at what is ultimately declared the disease specific RP2D prior to commencing dose expansion at the same dose.

The target toxicity rate is 0.25. A true toxicity rate of  $0.6 \times$  the target rate or lower is deemed potentially subtherapeutic such that dose escalation is indicated and a true toxicity rate of  $1.4 \times$  the target rate or higher is deemed overly toxic such that de-escalation is indicated. For non-informative priors, the prespecified optimal escalation and de-escalation boundaries for the observed toxicity rate are 0.197 and 0.298, respectively. Hence, if the observed toxicity rate at the current dose level is  $\leq 0.197$ , then the dose is escalated for the next cohort. If the observed toxicity rate is  $\geq 0.298$ , then the dose is de-escalated for the next cohort. Furthermore, if there is a higher than 95% posterior probability that the true toxicity rate associated with the current dose level is above the target toxicity rate, then that dose level and higher dose levels will be eliminated. These boundaries produce the following decision table based on the cumulative number of subjects who experience a DLT at current dose level (Table 1).

**Table 1. Dose De-escalation/Escalation Decision Rules**

| Action                                                 | # of DLT-Evaluable Subjects at Current Dose Level |   |   |   |   |   |   |   |    |    |    |
|--------------------------------------------------------|---------------------------------------------------|---|---|---|---|---|---|---|----|----|----|
|                                                        | 2                                                 | 3 | 4 | 5 | 6 | 7 | 8 | 9 | 10 | 11 | 12 |
| Escalate if # of subjects with DLT $\leq$              | 0                                                 | 0 | 0 | 0 | 1 | 1 | 1 | 1 | 1  | 2  | 2  |
| Stay at current dose level if # of subjects with DLT = | -                                                 | - | 1 | 1 | - | 2 | 2 | 2 | 2  | 3  | 3  |
| De-escalate if #of subjects with DLT $\geq$            | 1                                                 | 1 | 2 | 2 | 2 | 3 | 3 | 3 | 3  | 4  | 4  |
| Eliminate if # of subjects with DLT $\geq$             | NA                                                | 3 | 3 | 3 | 4 | 4 | 4 | 5 | 5  | 6  | 6  |

DLT = dose-limiting toxicity; NA = not applicable

Dose escalation increments are based on a modified Fibonacci sequence that yield proportionally smaller increases at higher doses, as shown in Table 2. At the joint discretion of the investigators and the sponsor additional interval dose levels may also be explored but will continue to follow identical de-escalation/escalation decision rules. If the BOIN rules recommend dose de-escalation, the next dose evaluated could be an intermediate dose not exceeding the current dose. If the BOIN rules recommend dose escalation, the next dose evaluated could be an intermediate dose not exceeding the next dose level in the modified Fibonacci sequence, chosen in consideration of all available information.

**Table 2. Proposed Dose Levels**

| Dose Level   | 1    | 2    | 3    |  |  |  |  |  |  |  |  |
|--------------|------|------|------|--|--|--|--|--|--|--|--|
| Dose (mg/kg) | 0.16 | 0.32 | 0.53 |  |  |  |  |  |  |  |  |

Throughout all parts of the study, ABBV-467 will be administered with an abbreviated dose ramp-up, in which 50% of the target dose will be administered on Cycle 1 Day 1 (C1D1), and full target dose thereafter (weekly until disease progression, unacceptable toxicity, or withdrawal of consent).

For each dose level, the second subject will not be dosed until at least 48 hours have elapsed since the initial dose for the first subject at that dose level.

### Part A and Part C

Subjects with R/R MM (Part A) will receive escalating doses of ABBV-467 as described above. Once a pharmacologically and/or clinically active and tolerable dose is identified based on review of totality of safety, efficacy, PK and PD data, this dose will be used to commence dose escalation in R/R AML (Part C), where provisional dose de-escalation will also be permitted.

In order to be considered DLT evaluable, a subject must either:

1. receive each of planned doses *and* at least 80% of the total planned dose of ABBV-467 for Cycle 1; or
2. experience a DLT after receipt of at least one dose of ABBV-467 during the DLT evaluation period.

Selection of doses used in the study, including the optimal biological dose (OBD) and RP2D, can be found in Section 4.2.

### Expansion Components

Dose expansion for subjects with R/R MM (Part B) or R/R AML (Part D) will commence after the RP2D is identified and the initial safety and efficacy data of ABBV-467 are evaluated as favorable by the Sponsor with input from the investigators. A cumulative review of safety, tolerability, efficacy, PK, and PD data collected during dose escalation will occur prior to initiating dose expansion.

Subjects with R/R MM (Part B) and R/R AML (Part D) will receive the ABBV-467 at the RP2D determined in Parts A and C, respectively. Expansion may occur at multiple dose levels and/or schedules. The expansion component will target enrollment of 20 response-evaluable subjects (with a maximum of 24 subjects enrolled regardless of response evaluability) per cohort to further evaluate the safety profile, and preliminarily evaluate efficacy, of ABBV-467 at RP2D.

At the joint discretion of the sponsor and the investigators, subjects may be prospectively selected for Parts B and D based on any of the following:

1. Only those with prior exposure to a BCL-2 inhibitor.
2. Only those naïve to prior BCL-2 inhibitor.
3. Irrespectively of prior BCL-2 inhibitor exposure.

## 4.2 Discussion of Study Design

---

### Choice of Control Group

Not applicable.

---

### Appropriateness of Measurements

Standard PK, statistical, clinical, and laboratory procedures will be utilized in this study. All efficacy measurements in this study are standard for assessing disease activity in subjects with MM and AML. All clinical and laboratory procedures in this study are standard and generally accepted.

### Suitability of Subject Population

Subjects with MM whose disease has relapsed after, or was refractory to, treatment with standard therapies (immunomodulatory agents, proteasome inhibitors, anti-CD38 monoclonal antibodies, alone or in combination) have limited options and poor prognoses. In addition, subjects with AML that have relapsed after 1 or more lines of treatment, including all locally approved therapies, face a dire prognosis, with survival measured in months or even weeks. These subjects are broadly considered ideal candidates for novel treatment approaches, and are therefore, the subject population chosen for this study.

### Selection of Doses in the Study

The starting dose of ABBV-467 is based on the International Conference on Harmonisation of Technical Requirements for Registration of Pharmaceuticals for Human Use (ICH) S9 guidance (ICH 2010). The dog is considered the appropriate species for calculating human starting dose.

Full pharmacology and toxicology data for ABBV-467 are provided in the ABBV-467 Investigator's Brochure.

## 5 STUDY ACTIVITIES

### 5.1 Eligibility Criteria

---

Subjects must meet all of the following criteria in order to be included in the study. Anything other than a positive response to the questions below will result in exclusion from study participation.

#### Consent

- ✓ 1. Subjects or their legally authorized representative must voluntarily **sign and date an informed consent**, approved by an independent ethics committee (IEC)/institutional review board (IRB), prior to the initiation of any screening or study-specific procedures.

#### Demographic and Laboratory Assessments

- ✓ 2. At least 18 years old.
- ✓ 3. Eastern Cooperative Oncology Group (ECOG) performance status 0, 1, or 2.
- ✓ 4. **Laboratory values** meeting the following criteria during the screening period prior to first dose of study drug:
  - For subjects with AML, the following hematologic parameter requirements are not applicable. For subjects with MM, subjects must have adequate hematologic function, defined as follows:
    - Absolute neutrophil count  $\geq 1000/\text{mm}^3$ ;
    - Platelet count  $\geq 75,000/\text{mm}^3$ ;
    - Hemoglobin  $\geq 8 \text{ g/dL}$ ;
  - Serum alanine aminotransferase (ALT)  $\leq 2.5 \times$  upper limit of normal (ULN);
  - Serum aspartate aminotransferase (AST)  $\leq 2.5 \times$  ULN;
  - Total bilirubin  $\leq 1.5 \times$  ULN (subject with documented Gilbert's syndrome may have a total bilirubin  $>1.5 \times$  ULN);
  - Amylase  $\leq 2 \times$  ULN;
  - Lipase  $\leq 2 \times$  ULN;
  - Creatinine clearance (CrCl)  $\geq 60 \text{ mL/min}$ , measured by 24-hour urine collection or calculated using the Cockcroft-Gault formula.
- ✓ 5. Echocardiogram with ejection fraction  $\geq 50\%$  and no other clinically significant finding that would increase the subject's susceptibility to cardiac toxicity.
- ✓ 6. No clinically relevant or significant ECG abnormalities, including ECG with QT interval corrected for heart rate (QTc) using Fridericia's formula (QTcF)  $> 450 \text{ msec}$  (males) or  $> 470 \text{ msec}$  (females).
- ✓ 7. Willingness and ability to comply with procedures required in this protocol.

## Disease Activity

- ✓ 8. Documented diagnosis of MM (Parts A and B only).
- ✓ 9. For MM subjects only: measurable disease, defined as at least 1 of the following:
  - Serum monoclonal protein  $\geq 1$  g/dL
  - Urine M-protein  $\geq 200$  mg/24 hours
  - Serum immunoglobulin free light chain (FLC)  $\geq 10$  mg/dL (100 mg/L), provided serum FLC ratio is abnormal
- ✓ 10. For MM subjects only: Subjects who have relapsed after or are refractory or intolerant to all established MM therapies that are both known to provide clinical benefit, and locally available. At least 3 prior lines of therapy must have been administered ([Appendix E](#)), including 1 or more immunomodulatory agents (e.g., lenalidomide or pomalidomide), 1 or more proteasome inhibitors (e.g., bortezomib or carfilzomib), and 1 or more anti-CD38 monoclonal antibodies (e.g., daratumumab).
- ✓ 11. Documented diagnosis of AML (Parts C and D only; subjects with APL are excluded throughout the study).
- ✓ 12. AML subjects only: Total white blood cell count  $< 25,000/\text{mm}^3$  (Note: hydroxyurea is permitted to meet this criterion).
- ✓ 13. For AML subjects only: failure to respond to, and/or relapse or progression after, at least 1 prior line of therapy, including all available standard therapies (per assessment of local investigator). Where applicable, this could include prior exposure to approved inhibitors of FLT3, IDH1, and IDH2.
- ✓ 14. No autologous stem cell transplant within 90 days prior to start of ABBV-467.
- ✓ 15. No allogeneic stem cell transplant within 180 days prior to start of ABBV-467.
- ✓ 16. No clinically significant graft versus host disease requiring ongoing systemic therapy.

## Subject History

- ✓ 17. No unresolved clinically significant non-hematologic toxicity of  $\geq$  Grade 2 from prior anticancer therapy.
- ✓ 18. No history of acute or chronic pancreatitis.
- ✓ 19. No significant unresolved liver disease. Subjects with hepatitis C who have received definitive treatment and are considered cured will be eligible.
- ✓ 20. No known history of hepatitis B or HIV infection. Testing for hepatitis B and HIV are not required as part of Screening.
- ✓ 21. No major surgery within 4 weeks of study treatment.
- ✓ 22. No history of central nervous system involvement by underlying disease.
- ✓ 23. No history of plasma cell leukemia.

- ✓ 24. No history of clinically significant medical conditions or any other reason that the investigator determines would interfere with the subject's participation in this study or would make the subject an unsuitable candidate to receive study drug.
- ✓ 25. No history of other malignancies, with the following exceptions:
  - No known active disease present within 3 years prior to first dose of study treatment, and felt to be at low risk of recurrence by the treating investigator;
  - Adequately treated in situ carcinoma without evidence of disease;
  - Basal cell carcinoma of the skin or localized squamous cell carcinoma of the skin without evidence of disease;
- ✓ 26. No history of an allergic reaction or significant sensitivity to constituents of the study drug (and its excipients) and/or other products in the same class.

### Contraception

- ✓ 27. For all females of child-bearing potential; a **negative serum pregnancy test** at the Screening Visit and a negative urine pregnancy test at baseline prior to the first dose of study drug.
- ✓ 28. Female subjects of childbearing potential must practice at least 1 protocol-specified **method of birth control**, that is effective from C1D1 through at least 185 days after the last dose of study drug (refer to Section 5.2).
- ✓ 29. Female must not be **pregnant, breastfeeding (even if breastfeeding is interrupted), or considering becoming pregnant** during the study or for approximately 185 days after the last dose of study drug.
- ✓ 30. **If male**, and subject is **sexually active with female partner(s) of childbearing potential**, he must agree, from C1D1 through 95 days after the last dose of study drug, to practice the protocol-specified contraception (refer to Section 5.2).
- ✓ 31. Male must not be considering **fathering a child or donating sperm** during the study or for approximately 95 days after the last dose of study drug.

### Concomitant Medications

- ✓ 32. Subject has no prior exposure to any targeted MCL-1 inhibitor.
- ✓ 33. Subject must not have been treated with **antineoplastic therapy** (including cytotoxic, targeted, and/or investigational therapy; but not including corticosteroids), within 28 days or 5 half-lives, whichever is shorter, prior to first dose of study drug and through the last dose of study drug(s).
- ✓ 34. No anticipation of the use of prohibited medications during study participation (see Section 5.3 for additional prohibited medications or foods).
- ✓ 35. Subject must not have received any live vaccine within 2 weeks before the first dose of study drug or be expected to need a live vaccination during study participation including at least 4 weeks after the last dose of study drug.

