#### Why Is This Study Being Conducted

Although remarkable advances in multiple myeloma (MM) have emerged with the introduction of several new, more effective, and less toxic therapies, it remains an incurable disease. Treatment paradigms for MM include immunomodulatory agents, proteasome inhibitors, monoclonal antibodies, and corticosteroids, often in 2- or 3-drug combinations. However, the majority of patients will eventually relapse after, or become refractory to, all available therapies, in which case prognosis is poor. There remains a clear unmet need to identify agents with novel mechanisms of action for use alone and in combination with existing standards of care, to improve outcomes for patients with MM.

Acute myeloid leukemia (AML) is a heterogeneous disease characterized by high unmet need. Current treatment strategies are still largely based on combination chemotherapy and stem cell transplantation, but the toxicities associated with this approach limits its utility in elderly and unfit patients, and outcomes for all patients with relapsed/refractory (R/R) AML are poor. As therapeutic progress in AML has been modest, opportunities for novel agents offering improved efficacy, reduced toxicity, or both, remain.

Myeloid cell leukemia-1 (MCL-1), a member of antiapoptotic B-cell lymphoma-2 (BCL-2) family proteins, is a key regulator of cell survival and homeostasis. Frequent overexpression of MCL-1 has been observed in multiple cancer types where it acts as a resistance factor to various chemotherapeutic and targeted agents. Therapeutic targeting of MCL-1, alone and in combination with other standard-of-care agents, enhances apoptotic death in preclinical MM and AML models, and offers a novel approach to treating these hematologic malignancies with progressive morbidity and eventual mortality.

ABBV-467 is a small molecule that potently and selectively binds and inhibits MCL-1. The first-in-human study will evaluate the safety and tolerability of ABBV-467 in subjects with either R/R MM or R/R AML. Based on the monotherapy data from this study, combination therapy with additional compounds may be explored in the future.

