## 5.3 Prohibited Medications and Therapy

---

No anticancer agents, radiation, anticancer medicinal/herbal remedies, investigational agents, anticancer corticosteroid therapy, or anticancer hormonal therapy may be taken while the subject is in the treatment phase of the study. However, during the dose escalation part of the study only, localized radiation therapy to a site of pre-existing and/or symptomatic disease may be permitted. Following approval from the sponsor, a subject may initiate or continue with protocol therapy without interruption during the course of palliative radiation therapy if the investigator believes that the risk of excessive bone marrow suppression or other toxicity is acceptable, and it is in the best interest of the subject.

Extramedullary sites of MM or AML identified at baseline that are surgically resected or in any radiated fields should be excluded from further response assessments.

Use of radiotherapy or surgical intervention must be recorded on the electronic case report form (eCRF).

Medications known to prolong the QT interval (Operations Manual Section 7.6) are prohibited.

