## 5.4 Prior and Concomitant Therapy

---

Any medication or vaccine (including over the counter or prescription medicines, vitamins, and/or other supplements) that the subject is receiving at the time of enrollment or receives during the study must be recorded through the follow-up visit.

Best supportive care and treatment in accordance with standard practice (antiemetics, antibiotics, transfusions, oxygen therapy, nutritional support, palliative treatment for pain or cough, etc.) will be given as appropriate to each subject. Any questions regarding concomitant or prior therapy should be raised to the AbbVie emergency contact. Information regarding potential drug interactions with ABBV-467 can be located in the ABBV-467 Investigator's Brochure.

Medications that may be required during the first 15 days of Cycle 1 to reduce the risk of tumor lysis syndrome (TLS) include the following:

- Allopurinol or other appropriate TLS risk-reducing agent required through Day 15 of Cycle 1.
- Adequate fluids to ensure dehydration prevention (note: per institutional standards while using medical judgment; refer to [Appendix G](#)).

In addition, use of hydroxyurea is recommended as needed to maintain a white blood cell count of < 25,000/ $\mu$ L during Cycle 1 of the study.

MM subjects only: In dose escalation, hematopoietic growth factors and transfusion support should not be given during the DLT evaluation period, but are otherwise permitted at the investigator's discretion, in accordance with local or institutional guidelines and/or practice patterns.

The following medications are to be used with caution during the study (see Operations Manual Section 7.5 for examples of each):

- P-glycoprotein inhibitors.
- Breast cancer resistance protein inhibitors.
- OATP1B1/B3 inhibitors.
- OATP1B1/1B3 substrates.
- Strong CYP3A4 inhibitors.

Subjects who are receiving corticosteroids chronically (> 3 months) for non-oncological purposes may continue at a dose that does not exceed 5 mg per day of prednisone or equivalent.

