### Multiple Myeloma Assessments

Disease assessments will be performed at the visits indicated in Section 2. MM subjects will be evaluated using the adapted International Myeloma Working Group (IMWG) 2016 criteria (see Section 7.3). Note that serum and urine for IMWG assessments do not need to be collected at C1D1 if the Screening samples were collected within 7 days of C1D1.

All subject's IMWG laboratory assessments (serum protein electrophoresis [SPEP], urine protein electrophoresis [UPEP], serum and urine immunofixation, serum free light chains, and serum quantitative immunoglobulins) will be performed by central laboratory, however, local labs may be performed at the investigator's discretion. All local laboratory results must be entered into the eCRF. Imaging and bone marrow assessments will be performed locally. Disease status should continue to be collected for MM subjects after study drug discontinuation for reasons other than disease progression.

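### Criterion 33 exempts corticosteroids without limit, and the 7-day waiver of the C1D1 myeloma samples lets a pre-dose steroid course fall between the baseline value and the first dose

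*Protocol*

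**What the plan says.** **Corticosteroids.** Protocol Section 5.1, criterion 33, sets out which earlier treatment is barred ahead of dosing in these terms: "including cytotoxic, targeted, and/or investigational therapy; but not including corticosteroids), within 28 days or 5 half-lives, whichever is shorter". It extends the restriction through the last dose. The key eligibility criteria in the synopsis carry the same exemption.

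Section 2.1 names the exempted class as myeloma treatment: "Treatment paradigms for MM include immunomodulatory agents, proteasome inhibitors, monoclonal antibodies, and corticosteroids".

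Section 5.3 lists among the things that may not be used "anticancer corticosteroid therapy, or anticancer hormonal therapy may be taken while the subject is in the treatment phase of the study". Criterion 34 excludes subjects expected to need prohibited medication during participation and points to Section 5.3. Section 5.4 adds that subjects on long-term steroids for non-oncological reasons "may continue at a dose that does not exceed 5 mg per day of prednisone or equivalent".

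**Myeloma baseline.** Operations Manual Section 3.16 gives this waiver, counted back from the first dosing day: "serum and urine for IMWG assessments do not need to be collected at C1D1 if the Screening samples were collected within 7 days". The C1D1 notes in Operations Manual Section 2.1 say the same. Otherwise, C1D1 serum and urine tests are scheduled.

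**Hydroxyurea.** Criterion 12 sets a white cell limit for AML with "Note: hydroxyurea is permitted to meet this criterion". Section 5.4 says that "use of hydroxyurea is recommended as needed to maintain a white blood cell count" below the same limit in Cycle 1. Neither criterion 33 nor Section 5.3 makes an exception for it.

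**The concern.** The class left out of criterion 33 is one that the protocol itself calls active against myeloma. Myeloma response is read mainly from the fall in M-protein or free light chains (Operations Manual Section 7.3: at least 50% in serum M-protein for partial response, at least 25% for minimal response, each with further conditions). There is no control group, so a fall caused by a recent steroid course cannot be subtracted from the one caused by ABBV-467. If the baseline sample is drawn before such a course and not repeated, the steroid effect becomes part of the measured change and can count toward the overall response rate (ORR) or the clinical benefit rate (CBR).

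Separately, a site reading criterion 33 alone finds corticosteroids exempt through the last dose, while Section 5.3 bans their anticancer use on treatment. The hydroxyurea passages have the same kind of gap.

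**Working it through.** **1. The steroid passages side by side**

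| Period | Anticancer corticosteroids | Non-oncological corticosteroids |
|---|---|---|
| Before C1D1 | Exempt under criterion 33; no other section applies | Exempt under criterion 33 |
| Treatment phase | Exempt under criterion 33; banned by Section 5.3, and criterion 34 refers to that ban | Exempt under criterion 33; long-term use capped in Section 5.4 |

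During treatment, the wording conflicts but the ban in Section 5.3 still operates. Before C1D1 nothing operates for anticancer use.

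**2. The baseline window**

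Screening runs from Day -21 to Day -1. If the myeloma samples are taken within 7 days of C1D1, the C1D1 set may be omitted and the Screening value is then the only scheduled pre-dose value. A course lying wholly between that sample and the first dose must fit into 7 days or less. Neither the response criteria (Operations Manual Section 7.3) nor the efficacy analysis (Protocol Section 7.3) has a rule for steroids given before the first dose. The requirement of two consecutive assessments and the censoring of response duration both refer to new therapy started later.

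**3. The plan's own figures**

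Table 5 gives one-sided exact 80% lower bounds for n = 20. The Clopper-Pearson bound for r responders is L = the 0.20 quantile of Beta(r, n - r + 1).

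| r of 20 | Table 5 | Recomputed |
|---|---|---|
| 5 | 0.158 | 0.1584 |
| 6 | 0.201 | 0.2013 |
| 7 | 0.245 | 0.2454 |
| 8 | 0.291 | 0.2906 |
| 10 | 0.384 | 0.3840 |

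All five reproduce, so no stated figure is wrong.

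**4. What one responder is worth**

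Section 7.7 uses 25% (5/20) as its example, because the bound excludes 15%. With one responder fewer, r = 4 gives the 0.20 quantile of Beta(4, 17) = 0.117, which does not exclude 15%. The two-sided 90% intervals that Section 7.3 will report move from 0.104 to 0.456 (5/20) to 0.071 to 0.401 (4/20). One responder is 1/20 = 5 percentage points, or 1/24 = 4.2 points if all 24 enrolled subjects are in the all-treated denominator.

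**5. Sensitivity, on an assumed input**

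Let p be the true drug response rate and s the share of drug non-responders who reach partial response through steroid effect. The observed rate is then q = p + (1 - p)s. The documents give no value for s; 0 to 10% is assumed only to show the direction.

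| p | s | q | P(at least 5 of 20) |
|---|---|---|---|
| 0.15 | 0 | 0.150 | 0.170 |
| 0.15 | 0.05 | 0.1925 | 0.338 |
| 0.15 | 0.10 | 0.235 | 0.523 |
| 0.10 | 0 | 0.100 | 0.043 |
| 0.10 | 0.05 | 0.145 | 0.153 |
| 0.10 | 0.10 | 0.190 | 0.327 |

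**The case against.** Several stronger readings are tempting, and the documents do not support them.

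- A reader might infer that criterion 33 opens the door to anticancer steroids on treatment. It does not: exemption from one list is not permission, and Section 5.3 with criterion 34 still bars that use. Nor does Section 5.3 prohibit corticosteroids as such; it bans anticancer use only.
- A reader might set a steroid-free interval of 0 days against 28 days for other agents. That ignores the alternative of 5 half-lives if shorter. The documents give no steroid half-life; assuming 3 to 36 hours, 5 half-lives is 15 to 180 hours, or about 0.6 to 7.5 days. The contrast with 28 days is not a fair measure of the gap.
- A reader might infer that the Part C starting dose could be set by a steroid artefact. Section 4.1 bases that choice on safety, efficacy, PK and PD together, and on a dose that is pharmacologically and/or clinically active.
- A reader might infer that an AML subject on hydroxyurea is both eligible and ineligible. That follows only if hydroxyurea counts as barred therapy and the specific allowances in criterion 12 and Section 5.4 are ignored. It is a wording conflict without bearing on M-protein.

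The remaining route is also narrow. Criterion 10 requires disease that has exhausted established therapy, with at least three prior lines, so a large fall after a short course is not a given. Response needs two consecutive assessments, and these are scheduled on Day 1 of 28-day cycles. Operations Manual Section 3.3 has all medication recorded from 4 weeks before screening, with dates and reason, so exposed responders can be identified. Efficacy is secondary and no hypothesis is tested.

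All of this stands, and it limits the likely size. It does not close the gap: confirmation makes a transient effect less likely to count but does not exclude it, and a medication record cannot supply the baseline value that was never drawn.

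**Conclusion.** The point holds in a limited form. Criterion 33 and the synopsis exempt corticosteroids without bounds, which conflicts in wording with Sections 5.3 and 5.4. The route to bias is pre-dose, applies to myeloma only, and arises where the 7-day waiver leaves a course of at most 7 days unmeasured between the baseline value and the first dose. Its direction is toward higher ORR and CBR, in a cohort without a control.

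Its size is unknown. The documents do not say how often steroids would be given in that window or how far M-protein would fall. The shift from 0.158 to 0.117 shows how sensitive the protocol's own example is to a single responder; it does not estimate the bias. The probabilities under assumed s likewise show direction only. The conclusion also assumes that the Screening value serves as the response baseline when the C1D1 samples are omitted.

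The change is worth making because it is cheap, not because a large distortion has been shown.

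**What to change.** 1. In Operations Manual Sections 2.1 and 3.16, remove the 7-day waiver for any myeloma subject given corticosteroids after the Screening sample, and name the C1D1 pre-dose M-protein or free light chain value as that subject's response baseline. Cost: one repeat blood and urine sample, already on the schedule by default, in a few subjects. Limit: steroid effect that continues after C1D1 would still be counted.
2. Reconcile criterion 33 and the synopsis with Sections 5.3 and 5.4 on corticosteroids, so that one reading applies before the first dose and during treatment.
3. Reconcile criterion 33 and Section 5.3 with criterion 12 and Section 5.4 on hydroxyurea, by cross-reference.

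Items 2 and 3 cost amendment wording only. Which clinical rule applies, including whether and how pre-dose steroids are restricted, is for the sponsor to decide.
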